1  
2  
3  
4  
5

## PROTOCOL SUMMARY

Non-alcoholic fatty liver disease is the most frequent liver abnormality observed in overweight or obese children and is strongly associated with metabolic syndrome and insulin resistance. Therefore, the aims of this project are: (i) To evaluate the effect of a 22 weeks multidisciplinary intervention program on hepatic fat fraction in overweight or obese children and (ii) To examine the effect of the intervention on cardiometabolic risk factors, self-esteem and well-being. A total of 160 children, 9-11 years, will be recruited by paediatricians and randomly assigned to control (N=80) or intervention (N=80) groups. The control group will receive a family-based lifestyle and psychoeducation program (2 days/month), while the intervention group will attend the same lifestyle education and psychoeducation program plus the exercise program (3 days/week). The duration of training sessions will be 90min of exercise, including warm-up, moderate to vigorous aerobic activities, and strength exercises. The primary outcome is the change in hepatic fat fraction (magnetic resonance imaging, MRI). Secondary outcomes include cardiometabolic risk factors such as total and adiposity (dual X-ray absorptiometry), visceral adiposity (MRI), functional peak aerobic capacity (cardiopulmonary exercise testing), blood pressure, muscular fitness, speed agility, and fasting blood insulin, glucose, C-reactive protein, alanine aminotransferase, aspartate aminotransferase, gamma glutamyltransferase, lipid profile and psychological measurements (questionnaires). All the measurements will be evaluated at baseline prior to randomization and after the intervention. This study will provide insight in the efficacy of a multidisciplinary intervention program including healthy lifestyle education, psychoeducation and supervised exercise to reduce hepatic fat and cardiometabolic risk in overweight children.

**Trial registration:** NCT02258126

**Keywords:** fatty liver, obesity, children, exercise, metabolic syndrome

61    **LIST OF ABBREVIATIONS**

62    ALT: alanine aminotransferase; AST: aspartate aminotransferase; BMI: body mass  
63    index; CRP: C-reactive protein; Gamma-GT: gamma glutamyltransferase; LDL: low  
64    density lipoprotein cholesterol; NAFLD: non-alcoholic fatty liver disease; TG:  
65    triglycerides; VCO2: carbon dioxide production; VO2max: maximum oxygen  
66    consumption.

67

## BACKGROUND

Childhood obesity is a global epidemic and a major public health problem (1). In Europe, as well as in other developed countries, the prevalence of paediatric overweight is ranging from 20% to 40%. Spain, together with other countries surrounding the Mediterranean Sea, shows the highest rates of this well-recognized public health problem (2).

There has also been a concomitant rise of health complications associated with excess adiposity including dyslipidemia, hypertension, abnormal glucose tolerance, reduced quality of life and psychological distresses (3). The rise in the prevalence rates of overweight in childhood which occurred in the last two decades may explain the emergence of non-alcoholic fatty liver disease (NAFLD) as the leading cause of chronic liver disease in developed nations (4, 5). The real prevalence of pediatric NAFLD is still not defined because (i) to date only a few population studies have been conducted in children and (ii) because of the different screening/diagnosis method used. Moreover, sex and ethnic differences have also been reported (6). Likewise, previous studies estimated that up to 70-90% of obese youths aged 2 to 19 years were affected by NAFLD (7). A children's autopsy study conducted to estimate the prevalence of NAFLD in the United States observed that 38% of obese children were affected by NAFLD (8). The condition of NAFLD in children is still under-diagnosed because paediatric patients are often asymptomatic, and liver enzyme levels are usually mildly elevated in NAFLD in children and may remain normal, even with biopsy proven hepatic steatosis (9, 10).

Paediatric NAFLD is strongly associated with several factors of metabolic syndrome such as insulin resistance, abdominal adiposity, hypertension and dyslipidaemia (5, 11, 12). Therefore, NAFLD has been considered the hepatic manifestation of metabolic syndrome (13). Strategies to reduce or prevent NAFLD in

94 overweight children have the potential to improve overall cardiometabolic risk and  
95 reduce the risk to develop cardiovascular disease, type 2 diabetes and liver dysfunction  
96 (14).

97         There is evidence that sedentary lifestyle and unhealthy diets are driving the  
98 obesity epidemic and its co-morbidities in children. In turn, lifestyle interventions  
99 including family-based nutritional education, psychoeducation, and physical activity are  
100 recognized as key factors in the obesity treatment or prevention in paediatric population  
101 (15-18). Moreover, interventions including exercise have the potential to improve  
102 psychological aspects such as self-esteem and well-being in overweight children (19).

103         Currently, there are no dietetic and physical activity guidelines for the  
104 management of NAFLD in children (20). In adults, weight loss is able to attenuate or  
105 even reverse the course of NAFLD (21). However, energy restriction programs may  
106 lead to undesirable loss of lean mass and could compromise healthy growth and  
107 development in children. Previous studies in children have shown that exercise reduces  
108 cardiometabolic risk factors such as visceral adiposity and insulin resistance (22), low  
109 density lipoprotein cholesterol (LDL) and triglycerides (TG) levels (23) or blood  
110 pressure (24). The majority of the exercise-based intervention studies focused on  
111 hepatic steatosis have been conducted in adults. As far as we are aware, there are only  
112 three previous studies in adolescents examining the effect of supervised exercise  
113 without caloric restriction on hepatic fat, and no one in pre-pubertal children (25-27).  
114 Given that: (i) multidisciplinary approaches to change or prevent unhealthy lifestyle  
115 targeting on modifiable factors are critical to improve obesity related disorders,  
116 especially in the long-term, and (ii) exercise has been associated with improvements in  
117 fatty liver, we propose a multidisciplinary intervention program including family-based

118 nutritional education, psychological education, and supervised aerobic and strength  
119 activities to reduce hepatic fat accumulation in overweight pre-pubertal children.

120

## 121 Hypothesis

122 Aerobic and strength training together improves insulin sensitivity and reduces visceral  
123 adiposity in overweight children. Given that hepatic fat accumulation is strongly linked  
124 to visceral adiposity and insulin resistance, our hypothesis is that a multidisciplinary  
125 intervention program including supervised aerobic and strength training will reduce  
126 hepatic fat fraction in overweight children.

127

## 128 Objectives

129 The primary objective of the EFIGRO study is to investigate the additional effect of  
130 aerobic and strength training on hepatic fat fraction in overweight and obese children  
131 participating in a 22 weeks family-based healthy lifestyle education and  
132 psychoeducation program.

133 Secondary objectives of the study are (i) to examine the additional effect of aerobic and  
134 strength training on cardiometabolic risk in overweight and obese children participating  
135 in a 22 weeks family-based healthy lifestyle education and psychoeducation program  
136 and (ii) to evaluate the additional effect of the exercise intervention in self-esteem and  
137 well-being of overweight and obese children.

138

## 139    **Methods**

### 140    **Study design**

141    The present study is a RCT (ClinicalTrials.gov ID: NCT02258126). All parents or  
142    guardians sign an informed written consent and all the children give their assent before  
143    being enrolled in the study. The study protocol has been approved by the Ethic  
144    Committee of Clinical Investigation of Euskadi (PI2014045). Since growing children  
145    are increasing in body size and undergoing developmental changes, a control group is  
146    necessary to detect changes due to training. Therefore, we compare relative changes  
147    between control and exercise groups. After baseline measurements, children are  
148    randomly allocated to the control or exercise group. Participants are followed for 22  
149    weeks. All families enrolled in the study participate in a lifestyle education and  
150    psychoeducation programs. The intervention is performed in waves so that each wave  
151    has from 15 to 20 participants. Follow-up examinations are performed in the same  
152    settings, with the same instruments and by the same investigators as in the baseline  
153    measurements.

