### 175 Sample size calculation

176 Hepatic fat fraction is the primary outcome of this study. However, as there was no  
 177 previous information available in the scientific literature allowing us to perform  
 178 calculations, the required sample size was determined for secondary outcome variables  
 179 intimately associated to hepatic fat accumulation, i.e., visceral adiposity, insulin  
 180 resistance and total body fat. Likewise, we expect that pre-post intervention differences  
 181 in our design consisting in two experimental groups, control and exercise group, will  
 182 have a size effect ( $d$ -cohen) of 0.5 for visceral fat (N=64 in each group, 80% power and  
 183  $\alpha$  of 0.05 and 0.7 for insulin resistance and total body fat percent (N=34 in each group,  
 184 80% power and  $\alpha$  of 0.05). Previous studies have reported losses to follow-up between  
 185 4% and 17%. Assuming a maximum loss of follow-up of 20%, we plan to recruit a total

of 160 overweight children, 80 children for each group. These effect size estimates are based on previous studies performed in overweight children with similar age range and a similar intervention program (22, 29, 30).

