## Randomization

Eligible participants will be randomly assigned after completing the baseline measurements to either the control or exercise groups (Figure 1). Randomization of the participants into control or exercise group will be computer generated using IBM-SPSS-Statistical software. Assessment staff will be blinded to participant randomization assignment.

[figure not shown]

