## 566 Data analysis plan

567 The data analysis plan will be defined based mainly in two analyses: i) the per-protocol  
568 analysis, and ii) the intention-to-treat analysis (ITT). For reporting the main findings,  
569 we will use the per-protocol principle which includes children with overweight or  
570 obesity that completed pre and post intervention assessments, and attend at least 50% of  
571 the family-based lifestyle program (no minimum required for exercise program). We  
572 will focus on per-protocol principle because we are interested in knowing the “real”  
573 efficacy rather than effectiveness of our intervention. In addition to the per-protocol  
574 principle, we will also analyse the data using the ITT. Under this principle, we will use  
575 multiple imputation for observations lost at post intervention.

576 The baseline characteristics of the subjects’ in the two intervention groups will be  
577 compared using either the Student t test (for continuous variables) or the  $\chi^2$  test (for  
578 categorical variables). Differences between the intervention groups in terms of  
579 postintervention values for the primary and secondary outcomes will be also examined  
580 using the Student t test. Within group differences (pre vs. post values) in primary and  
581 secondary outcomes will be examined using the Student paired t test  
582 following per protocol and intention-to treat principles. In both the per protocol and the  
583 intention-to-treat analyses, differences between the control and exercise groups in terms  
584 of changes in primary and secondary outcomes will be examined by ANCOVA  
585 adjusting for baseline values. Cohen’s d will be used to estimate the effect size and 95%  
586 CI.

587 Significance will be set at  $P < 0.05$ . All calculations will be made using the Statistical  
588 Package for Social Sciences version 24.0 for Windows (SPSS Inc. Chicago, IL). We  
589 will also use R software (v.3.1.2) for analysis and figures.

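### Exercise and education run in waves of 15–20 children, but the stated randomisation and ANCOVA make no use of wave; some balance and precision are given up, though standard errors stay valid

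*Protocol*

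**What the plan says.** Study design (Protocol): "The intervention is performed in waves so that each wave" "has from 15 to 20 participants". In the same section, children are individually "randomly allocated to the control or exercise group" once baseline measurement is finished.

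Randomization: "Randomization of the participants into control or exercise group will be computer generated using IBM-SPSS-Statistical software". No block, stratum or wave is mentioned.

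Data analysis plan: differences between arms in terms "of changes in primary and secondary outcomes will be examined by ANCOVA" "adjusting for baseline values". The section on retention and adherence adds attendance as an adjustment variable. Wave appears in neither place.

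Sample size calculation: a standardised effect "of 0.5 for visceral fat (N=64 in each group, 80% power and" a significance level of 0.05, raised to 80 per group (160 in total) for 20% loss. The calculation treats children as independent. It is based on visceral fat because the protocol found no usable prior data on hepatic fat, the primary outcome.

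Two further passages bear on the point. Under Exercise training intervention, sessions are offered on five weekdays and each family picks three. Under Measurements, post-tests fall within three days of a child's last session, so outcome dates follow the wave calendar.

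**The concern.** A 22-week wave is a natural block in time. Children in one wave are likely to share a season and a stretch of the school year, and these can plausibly move activity, diet and body composition in both arms. Where such a block is known in advance, the usual practice is to balance allocation within it and to put it in the model. The protocol states an allocation method and an analysis model, and neither uses the block.

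At stake are the balance of arms within each wave and the share of outcome variance that lies between waves and stays in the error term. A separate issue arises because exercise is delivered in groups: children who train together may have correlated responses, in one arm only. That bears on the error rate, not just on precision.

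**Working it through.** **Inputs from the protocol.** 160 children, 80 per group; 20% loss; d = 0.5; 64 evaluable per group; 80% power; alpha 0.05 (sidedness not stated); waves of 15–20; ANCOVA on change with baseline as covariate.

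**Assumptions (the protocol gives no values).** Wave explains 5–10% of residual variance; ICC among children training together 0.02–0.05; allocation unblocked where stated.

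**1. The plan's own figure.** A two-sample t calculation at d = 0.5, two-sided 0.05 and 80% power gives 63.8, so 64 per group; 64/0.80 = 80. Power at 64 per group is 80.1%. The plan reproduces.

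**2. Number of waves.** 160/20 = 8 and 160/15 = 10.7, so 8 to 11 if a wave holds children of both arms.

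**3. Balance under simple randomisation.** For wave size n, the chance that the arms differ by 5 or more is P(|2X − n| ≥ 5) with X ~ Binomial(n, 0.5):

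| n | 15 | 16 | 17 | 18 | 19 | 20 |
|---|---|---|---|---|---|---|
| P | 0.302 | 0.210 | 0.332 | 0.238 | 0.359 | 0.263 |

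The range is 21–36%; the jumps mostly reflect odd and even n. Over the whole trial an exact 80/80 split has probability 0.063. The power cost of overall imbalance is small: 79.5% at 70/90 and 79.2% at 68/92, against 80.1%. A split as uneven as 68/92 or worse has probability 0.07.

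**4. Does omitting wave distort the standard error?** Simulation of 8 waves of 16 evaluable children, baseline-adjusted ANCOVA, 10,000 runs per setting, a wave effect common to both arms:

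| Allocation, model | Wave share | Empirical SE / model SE | Type I error | Power at d = 0.5 |
|---|---|---|---|---|
| Simple, no wave term | 5% | 0.178 / 0.178 | 0.053 | 0.797 |
| Simple, no wave term | 10% | 0.177 / 0.177 | 0.049 | 0.806 |
| Simple, wave term | 5% | 0.180 / 0.179 | 0.052 | 0.796 |
| Simple, wave term | 10% | 0.175 / 0.174 | 0.053 | 0.817 |
| Balanced by wave, no wave term | 5% | 0.175 / 0.177 | 0.047 | 0.819 |
| Balanced by wave, no wave term | 10% | 0.170 / 0.177 | 0.042 | 0.819 |
| Balanced by wave, wave term | 5% | 0.175 / 0.173 | 0.052 | 0.829 |
| Balanced by wave, wave term | 10% | 0.170 / 0.169 | 0.051 | 0.843 |

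Errors are correct in the first case and slightly conservative when allocation is balanced but wave is not modelled. From the first pair of rows to the last, power rises by 3.2 and 3.8 points. The wave term alone, on simple allocation, gains between nothing and 1 point, so most of the benefit needs both changes.

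**5. Closed-form check of the gain.** Removing a share s of residual variance multiplies d by 1/√(1 − s). At 64 per group and after spending the wave degrees of freedom, power is 82.1% for s = 0.05 and 84.1% for s = 0.10. Against 80.1% that is 2 to 4 points. Degrees of freedom: 128 − 3 = 125 before wave, less 7 (8 waves) to 10 (11 waves).

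**6. Clustering in the exercise arm.** Suppose training groups are half a wave less 20% loss: 7.5–10 children × 0.8 = 6–8 evaluable (m). With clustering in one arm, the variance of the difference is multiplied by V = [1 + 1 + (m − 1)ICC]/2. Type I error if ignored is 2[1 − Φ(1.96/√V)].

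- ICC 0.02, m = 6: V = 1.05, type I error 5.6%, power of a correctly sized test 78%.
- ICC 0.05, m = 8: V = 1.175, type I error 7.1%, power 74%.

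Simulation under simple allocation, with groups of about 8, gives 0.060 and 0.073 at these ICCs with wave ignored, and 0.058 and 0.076 with a fixed wave term. The wave factor therefore does not repair this.

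**The case against.** The strongest reply is that nothing here is an error. With individual randomisation, omitting a prognostic block costs precision but not validity, and step 4 confirms it. A reader might infer from the missing wave term that the standard errors are wrong; the documents do not support that. The inflated error rates in step 6 come from a different mechanism, correlated response among children who train together, for which the protocol gives no figure.

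A reader might also infer that the arms will be uneven. The protocol is silent on blocking rather than opposed to it, and its stated 80 per group fits a balanced list. Even under simple randomisation, overall imbalance costs under 1 power point up to 68/92.

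The protocol says only that the intervention is run in waves. That enrolment and measurement follow waves is an inference, strong for post-tests and weaker for enrolment. Because families choose three of five days, half a wave may not be a real training group. Follow-up also uses the same settings, instruments and investigators as baseline, which limits one source of drift.

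Finally, extra covariates and random effects are often left to a statistical analysis plan, which is not at hand. That carries weight for the clustering model. It carries less for the allocation method, which belongs in the protocol, and for the ANCOVA, whose adjustment the protocol itself states. Those two remain open to improvement.

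**Conclusion.** The point holds as a modest efficiency improvement to a stated method. The protocol plans waves and uses them in neither allocation nor analysis. If wave explains an assumed 5–10% of residual variance, blocking by wave together with a wave term is worth about 2–4 points of power. If allocation is simple, a wave of 15–20 has a 21–36% chance of arms differing by 5 or more children. The planned standard errors are not invalid for lack of a wave term.

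The clustering point is separate and conditional: type I error of about 5.6–7.1% and power of about 78–74%, if the ICC is 0.02–0.05 with 6–8 evaluable children per training group. With no such correlation, that concern disappears.

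Both sets of figures use the d = 0.5 set for visceral fat, since the protocol gives no effect size for hepatic fat. This is something to consider, not a defect that threatens the primary result.

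**What to change.** - **Randomization section:** for future waves, specify permuted blocks of varying size within each wave. If this is already done, say so. Cost: a new allocation list.
- **Data analysis plan:** add wave as a factor to the ANCOVA for primary and secondary outcomes. Cost: one model term, using 7–10 of about 125 degrees of freedom.
- **Sensitivity analysis, for clustering only:** fit a model with a random effect for the actual training group in the exercise arm and none in the control arm. Define groups from recorded session attendance, since waves and training groups may not coincide. Cost: recording which children train together, and one extra model.

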### 154    **Participants and selection criteria**

155    Participants are recruited from the Paediatric Endocrinology Unit of the University  
156    Hospital of Araba (HUA) (Vitoria-Gasteiz, Spain). Moreover, paediatricians in Vitoria-  
157    Gasteiz are invited to refer children meeting the inclusion criteria to the EFIGRO  
158    program. **Figure 1** shows planned flow diagram of the study participants from  
159    recruitment to the end of the intervention. Inclusion criteria include primary overweight  
160    or obesity status defined according to the International Obesity Task Force (28), aged  
161    between 9 and 11 years, and to have at least one parent or caregiver willing to  
162    participate in the program sessions. Exclusion criteria include medical conditions or  
163    medications that would affect study results or limit physical activity. Moreover, girls

164 who have already begun to menstruate at baseline are not eligible to participate in the  
 165 study (**Table 1**).

166 **Table 1.** Eligibility criteria for the EFIGRO study.

|     |                                                                                                     |
|-----|-----------------------------------------------------------------------------------------------------|
|     | Inclusion criteria                                                                           |
|     | Aged 9-11 years                                                                                     |
|     | Overweight or obesity status according to the International Obesity Task Force criteria             |
|     | To have at least one parent or caregiver willing to participate in the program sessions             |
|     | Exclusion criteria                                                                           |
|     | Not available for assessment session                                                                |
|     | In girls, begun to menstruate at baseline                                                           |
|     | Medical conditions or medications that would affect study results or limit physical activity |
| 167 | EFIGRO: the effect of exercise on hepatic fat on overweight children                                |

168 Before starting the study, a pre-screening appointment will be scheduled with the  
 169 investigation team to assess eligibility, family needs and commitment. Parents will  
 170 provide the child's health history and family history, and detailed contact information.  
 171 After completion of the informed consent process, children will undergo anthropometric  
 172 screening (height and body mass), and will be selected for inclusion in the study if they  
 173 are classified as overweight or obese. Moreover, all participants will undergo a  
 174 complete physical examination by the physician of the study.

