#### 514 **Potential confounders**

##### 515 *Pubertal development*

516 Pubertal development will be directly assessed according to Tanner criteria (genital  
517 development and pubic hair) by the paediatricians in the Paediatric Endocrinology Unit  
518 of the HUA.

519 *Physical activity, sedentary behaviour and dietary assessment*

520 Both the control and the exercise groups will attend the same healthy lifestyle education  
521 program. However, differences in changes in physical activity level, sedentary  
522 behaviour and dietary habits could be potential confounders on the effect of the  
523 intervention on hepatic fat and cardiometabolic risk factors.

524 Physical activity will be objectively measured by accelerometry. Children will be asked  
525 to wear an accelerometer on their non-dominant wrist (wActisleep-BT, USA) for seven  
526 consecutive days all the time, except for water-based activities. Thresholds will be used  
527 to classify raw counts per minute into intensities of physical activity (66). Information  
528 about sleep duration and quality will be also obtained from the accelerometers.

529 Participants will also complete a diary log. A self-reported sedentary behaviour  
530 questionnaire (67) will be administered to the children. Participants will report the  
531 frequency of specified sedentary behaviours using predefined response categories  
532 separately for weekdays and weekends. Behaviours to be assessed include watching TV,  
533 playing computer games, playing video games or phone games, surfing the Internet for  
534 recreation, surfing the Internet for study purposes, and studying (nonschool time).

535 Dietary intake will be evaluated by two non-consecutive 24h recalls within a period of  
536 seven days. Children will report all their food and beverage ingestions assisted by  
537 nutritionists. Moreover, dietary habits and patterns will be evaluated by two different  
538 food frequency questionnaires: the KidMed index for the children (68) and a validated  
539 food frequency questionnaire for the parents or caregivers (69). The KidMed index was

540 developed to estimate adherence to the Mediterranean dietary pattern in children and  
541 young adults, based on foods/dietary patterns that sustain it.

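### The Background calls the target children pre-pubertal but eligibility admits mixed pubertal stages, and the stated ANCOVA omits the Tanner stage that the protocol itself names a potential confounder

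*Protocol*

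**What the plan says.** **Rationale.** The Background section says that the three earlier studies of supervised exercise and liver fat were in adolescents and that none was in children before puberty. It then proposes a programme of education and supervised "activities to reduce hepatic fat accumulation in overweight pre-pubertal children".

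**Objectives.** The primary objective concerns the additional effect of "aerobic and strength training on hepatic fat fraction in overweight and obese children". The protocol summary, the hypothesis and the secondary objectives likewise speak of overweight, or overweight and obese, children. None has a pubertal qualifier.

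**Eligibility.** Table 1 in Participants and selection criteria requires "Aged 9-11 years" and overweight or obesity. Its only criterion on maturity is the exclusion "In girls, begun to menstruate at baseline". The text above the table repeats it: girls "who have already begun to menstruate at baseline are not eligible to participate in the" study. Screening then selects on height and body mass. A physical examination follows, with no pubertal threshold attached.

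**Measurement.** The table of measurements lists Tanner stage twice, under secondary outcomes and under potential confounders. The section on potential confounders says that paediatricians assess it directly.

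**Analysis.** Under the Data analysis plan, differences between the groups in terms "of changes in primary and secondary outcomes will be examined by ANCOVA", adjusted for baseline values. Tanner stage is not named there.

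**The concern.** The document describes its population in two ways. Menarche comes after puberty has begun, so excluding girls past menarche does not leave a pre-pubertal group of girls, and boys have no limit at all. Listing pubertal stage as a potential confounder only makes sense if stage is expected to vary among those enrolled. A reader who takes the evidence gap from the Background could therefore credit the overall result to pre-pubertal children, when it will come from a mixed group.

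The second part concerns the model. The trial already collects a maturity measure and regards it as related to outcome, but the stated ANCOVA does not use it. At stake is some avoidable residual variance in the primary and secondary comparisons.

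**Working it through.** **1. The plan's own figures.** Inputs from Sample size calculation: standardised effects of 0.5 (visceral fat) and 0.7 (insulin resistance, body fat percent), 80% power, alpha 0.05 (two-sided assumed), 20% loss.

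- Normal approximation, n per group = 2(1.96 + 0.84)²/d²: 63 for d = 0.5 and 33 for d = 0.7.
- Solved with the t distribution: 63.8, rounded up to 64, and 33.02, rounded up to 34. Both match the protocol.
- Allowance for loss: 64/(1 − 0.20) = 80 per group, 160 in total. This matches too.

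The sample size is therefore not in question here. It rests on an overall comparison, not on a pubertal subset.

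**2. Who can be enrolled.**

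| Child aged 9-11, overweight or obese | Eligible under Table 1? | Pre-pubertal, as in the Background? |
|---|---|---|
| Boy, Tanner 1 | Yes | Yes |
| Boy, Tanner 2 or higher | Yes | No |
| Girl, Tanner 1 | Yes | Yes |
| Girl, Tanner 2 or higher, before menarche | Yes | No |
| Girl after menarche | No | No |

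Two of the four eligible rows fall outside the Background's description. The documents give no Tanner distribution, so how many children that means is unknown. For illustration, with an assumed 30%, 50% or 70% already in puberty, the pre-pubertal number among 160 is 160 × 0.70 = 112, 160 × 0.50 = 80 or 160 × 0.30 = 48.

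**3. What adjustment would gain.** If baseline Tanner stage explains a share r of the residual variance left after the arm and the baseline outcome, the interval width is multiplied by √(1 − r).

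- r = 0.03 (assumed): √0.97 = 0.985, about 1.5% narrower.
- r = 0.08 (assumed): √0.92 = 0.959, about 4% narrower.

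In sample-size terms, 64/0.97 = 66.0 and 64/0.92 = 69.6, so the gain is worth about 2 to 6 extra completers per group. The price is one degree of freedom: with 128 completers, 124 residual degrees of freedom instead of 125.

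**4. What a Tanner stage 1 estimate could show.** With 64 completers per group, of whom an assumed share f are pre-pubertal, the power of a two-sided t-test at d = 0.5 is:

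| f | Completers per group | Power |
|---|---|---|
| 1.00 | 64 | 80% |
| 0.90 | 57.6 | 76% |
| 0.75 | 48 | 68% |
| 0.50 | 32 | 50% |
| 0.25 | 16 | 28% |

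The 0.5 is the protocol's effect size for visceral fat. The protocol states that it had no basis for an effect size on hepatic fat, so these figures do not carry over to the primary outcome without a further assumption.

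**5. Timing of the covariate.** The Measurements section exempts confounders such as pubertal development from being measured at baseline and repeated. The protocol summary places baseline measurement before randomisation. Read together, Tanner stage is most naturally a single assessment before randomisation, but no sentence says so outright.

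**The case against.** The strongest reply is that no formal claim about pre-pubertal children is made. The word carries weight only in the Background. The Discussion mentions prepubescent children in a general remark on weight goals and closes by speaking of overweight children. This stands. A reader might infer that the trial fails its stated purpose, or that its design is invalid, but the objectives match the eligible group and randomisation protects the comparison whatever the mix of stages.

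A reader might also infer that leaving Tanner stage out of the model biases the result. It does not: any baseline imbalance after randomisation arises by chance, so the case for adjustment is precision. Baseline adjustment also already absorbs the part of pubertal variation that shows in the baseline outcome, which is one reason to expect a small gain.

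A third reply is that covariates may be left to a statistical analysis plan that is not shown, and that the Data analysis plan is not a complete list, since the section on retention and adherence adds attendance as a confounder. This stands in part. The silence does not prove that pubertal stage will never be examined. But the protocol does state a model, says in another section that attendance enters the analyses, and nowhere says the same of Tanner stage. Proposing a better model than the one written is fair comment.

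Finally, a Tanner stage 1 subgroup with an interaction test is open to debate given the power above, and an interaction test would have less power still. It is not required here.

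**Conclusion.** The point holds as a mismatch between rationale and eligibility, together with a missed, inexpensive covariate. The wording inconsistency follows from the text alone. It limits what may be said about pre-pubertal children and leaves allocation, outcomes, sample size and the randomised comparison unaffected. The precision gain is modest, about 1.5-4% narrower intervals, and rests on an assumed 3-8% of residual variance for which the documents give no source. The pre-pubertal counts and subset powers likewise rest on assumed shares. The documents do not support saying that the trial is invalid, that its comparison is biased, or that it formally promises a pre-pubertal result.

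**What to change.** 1. Keep the eligibility criteria as they are.
2. In the Background, describe the population as children aged 9-11 years of mixed pubertal stage (girls pre-menarche), and do not present the overall result as evidence in pre-pubertal children.
3. In the Data analysis plan, add baseline Tanner stage (1 versus 2 or higher) as a prespecified ANCOVA covariate for the primary and secondary outcomes, with precision as the stated reason. Say that it is recorded before randomisation and how the two assessed criteria, genital development and pubic hair, give one stage. List it once in the table of measurements, as a baseline covariate.
4. If a Tanner stage 1 estimate is reported, label it exploratory and give its confidence interval.

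The cost is a few sentences and one degree of freedom. No new data and no change to recruitment are needed, provided that Tanner stage is recorded before randomisation.
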